#### Secondary Judgment Criteria

- Differentials of the MDP-QS and MDP- A2 subscales of the Multidimensional Profile of Dyspnea measured between before and after tDCS, in order to assess the effect of tDCS on the different components of dyspnea: sensory (MPD-QS) and emotional qualifiers (MPD-A2 subscales). Each experimental arm will be compared to the placebo group at risk 0.05 using a Student test. If the two experimental arms are greater than the placebo arm, they will be compared to each other at risk 0.05.- Differential in the IC-RDOS (intensive care respiratory distress observation scale) scale: between before and after the use of tDCS. A significant reduction in this score after the use of tDCS will translate into a reduction in respiratory discomfort, especially dyspnea. Each experimental arm will be compared to the placebo group at risk 0.05 using a Student test. If the two experimental arms are greater than the placebo arm, they will be compared to each other at risk 0.05.- Pre-inspiratory potentials (PPI): the possible presence of PPI on the EEG in this patients population could be a marker of respiratory suffering, and a possible disappearance of PPI after the use of tDCS could be interpreted as a relieving effect on breathing difficulty. Each experimental arm will be compared to the placebo group at 0.05 risk using a Fisher test. If the two experimental arms are greater than the placebo arm, they will be compared to each other at risk 0.05.- The respiratory parameters: mouth pressure (amplitude of variation), PetCO2, tidal volume (VT), and respiratory rate (F) as well as ventilation/minute (calculated from VT and F). The comparisons of each of these parameters will be carried out. Each experimental arm will be compared to the placebo group at risk 0.05 using a Student test. If the two experimental arms are greater than the placebo arm, they will be compared to each other at risk 0.05.- Evaluation of the impact of tDCS on the patient's future outcome during the 28 days following inclusion:
Death on D28 in intensive care and in the hospital: Each experimental arm will be compared to the placebo group at 0.05 risk using a Fisher test. If the two experimental arms are greater than the placebo arm, they will be compared to each other at risk 0.05. Kaplan-Meir curves for death.Cumulative incidence of delirium and its duration (CAM-ICU scale): The cumulative incidence estimates will be made using the gray method and compared according to the previous procedure using a gray test.Proportion of patients who failed to withdraw from mechanical ventilation on D28: Each experimental arm will be compared to the placebo group at 0.05 risk using a Fisher test. If the two experimental arms are greater than the placebo arm, they will be compared to each other at risk 0.05.Cumulative incidence of mechanical ventilation on D28: The cumulative incidence estimates will be made using the gray method and compared according to the previous procedure using a gray test.The duration of the resuscitation stay: Estimates of the median length of stay in intensive care will be made from an inverted Kaplan Meier estimator and compared according to the previous procedure using a log rank test.

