#### Inclusion Criteria

- Adult patient, hospitalized in intensive care for COVID-19, having required mechanical ventilation for at least 24 h.- Not sedated or having a good awakening (Richmond Agitation Score- Sedation Scale (RASS)> −3 at the time of inclusion (42) within 48 h of stopping sedation.- Able to answer yes or no to simple questions.- Having significant dyspnea (level≥ 4) on the A1 scale of the Multidimensional Profile of Dyspnea (MPD-A1≥ 4) (1, 41).- Signature of informed consent by the patient or his family member.

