#### Secondary Objectives

- To evaluate the effect of tDCS on the different components of dyspnea using the other subscales of the multidimensional profile of dyspnea “MPD”: sensory (MPD-QS) and emotional (MPD-A2) subscales.- To determine if tDCS also allowed a significant reduction in dyspnea measured by the IC-RDOS scale (intensive care respiratory distress observation scale) (43).- To investigate the presence of pre-inspiratory potentials (PPI) on the EEG in this patient population and determine the effect of tDCS on these PPIs in patients who may have them.- To evaluate the effect of tDCS on respiratory parameters: mouth pressure (amplitude of variation), PetCO2, tidal volume (VT), and respiratory rate (F) as well as ventilation/minute (calculated from VT and F).- To evaluate the impact of the possible relief of dyspnea by tDCS on the patient's close outcome during the 28 days following inclusion: mortality in intensive care, in hospital on D28, the cumulative incidence of delirium and its duration until D28, the cumulative incidence of mechanical ventilation, the failure to wean from mechanical ventilation on D28, and the length of stay in intensive care.

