#### Secondary Endpoints

- Differentials of the MDP-QS and MDP-A2 subscales of the Multidimensional Profile of Dyspnea measured between before and after tDCS: in order to assess the effect of tDCS on the different components of dyspnea: sensory (MPD-QS) and emotional qualifiers (MPD-A2 subscales).- Differential in the IC-RDOS (intensive care respiratory distress observation scale) scale between before and after the use of tDCS. A significant reduction in this score after the use of tDCS will translate into a reduction in respiratory discomfort, especially dyspnea.- Pre-inspiratory potentials (PPI) assessment: the possible presence of PPI on the EEG in this patient population could be a marker of respiratory suffering, and a possible disappearance of PPI after the use of tDCS could be interpreted as a relieving effect on breathing difficulty.- The respiratory parameters measurement: mouth pressure (amplitude of variation), PetCO2, tidal volume (VT), and respiratory rate (F) as well as ventilation/minute (calculated from VT and F), between before and after use of tDCS.- Evaluation of the impact of tDCS on the outcome of patients during the 28 days following inclusion:
Death by D28 in intensive care and in the hospital,Cumulative incidence of delirium and its duration (CAM-ICU scale) (44).Proportion of patients with mechanical ventilator dependance beyond D28.Cumulative incidence of mechanical ventilation on D28,The duration of the resuscitation stay.

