#### The Respiratory Parameters

The subject being connected to the ventilator, by measuring devices corresponding to a series connection which comprises—downstream of the subject—a device equipped with a CO2 sensor and a pneumotachograph, the pressure sensor of which also makes it possible to measure the mouth pressure (Pm) (NICO2 sensor combined CO2 adult flow Novametrix Nico).

The oxygen saturation will be determined with your finger using a pulse oximeter (Novametrix Oxymeter). The acquisition of all of these respiratory signals (Pm, instantaneous flow rate, expired CO2 and SatO2) is carried out during a period of 15 min before the introduction of tDCS, then again for 15 min after the end of tDCS.

The following respiratory parameters will be precisely measured and calculated:
- The pressure measured at the mouth (Pm), the amplitude of variation of which (aPm), gives an indirect but fairly practical reflection of the additional respiratory effort, which, in the case of dyspnea linked to laden breathing is one of the parameters that is best correlated with its intensity.- PETCO2: the partial pressure of CO2 at the end of expiration: by being (in the ideal case), a reflection of capnia, the increase of this being another mechanism inducing dyspnea with a strong unpleasant connotation (air hunger) especially in a context where ventilation is forced to a level lower than that which would have been chosen spontaneously. Thus, the measurement of aPm and PetCO2 will allow us to assess an equivalent of physical stimulus for each of the two types of dyspnea and to assess the relationship of these with the intensity of the dyspnea. In addition, in the case of aPm, it will provide an index of the motor response to the loads.- Tidal volume and respiratory rate as well as ventilation/minute (calculated from the instantaneous flow signal) will provide us with an interesting insight into the adaptation of breathing to the physiological mechanisms underlying dyspnea.

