#### Description of the Acts Performed and Devices Used

This is a clinical, interventional, bi-centric, randomized, single-blind, 3-arm trial, including a placebo-controlled arm, and 2 experimental arms, evaluating the effectiveness of a medical device for therapeutic purposes (tDCS) with 63 (3 groups of 21) patients on mechanical ventilation in intensive care with dyspnea. The primary endpoint will be assessed by an independent, blind observer. Transcranial stimulation will be delivered using a medical certified “Starstim 8” brain stimulator controlled via Bluetooth using a laptop computer (Neuroelectrics, Barcelona, Spain), Stimulation will delivered through traditional 5 × 7 cm rectangular sponge electrodes, with a contact area of 35 cm^2^ (Sponstim, Neuroelectrics, Barcelona, Spain). The tDCS will be applied upon the left hemisphere because of the functional dominance of this hemisphere in humans and in accordance with previous studies having evaluated the effect of tDCS on pain and the respiratory tract (27, 28, 32, 38, 51). As described in our previous work (38), two identical, rectangular, saline-soaked electrodes, each 7 cm long and 5 cm wide (35 cm^2^), were secured to the scalp. For anodal tDCS, the anode will be placed over the left diaphragmatic primary motor cortex (4 cm lateral to the midline and 1 cm anterior to the binaural line) and the cathode will be placed above the right orbit. These positions will be switched to obtain cathodal tDCS. For both anodal and cathodal tDCS, intensity will be 2 mA and the duration 30 min. The current density used will be 0.057 mA/cm^2^, which has been proven to be safe (52–55). For the sham condition (placebo tDCS), intensity was also 2 mA but duration was only 2 min. Nitsche and Paulus reported in 2000 that at least 3 min of tDCS was necessary to induce after-effects (31).

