#### Research Follow-Up Visits

The patients will then be followed for a period of 28 days after inclusion in order to collect the evolution data including: Death, measurement of delirium (CAM-ICU scale) until D28; ventilation status (spontaneous or mechanical) and withdrawal (in progress, successful, failure) until D28, the cumulative incidence of mechanical ventilation, and the length of stay in intensive care.

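### The secondary endpoint 'cumulative incidence of mechanical ventilation on D28' is, as worded, already met by every patient at inclusion, and the companion weaning-failure endpoint has three wordings

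*Protocol article*

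**What the plan says.** **Population.** The Inclusion Criteria admit adults in intensive care for COVID-19 "having required mechanical ventilation for at least 24 h"; Study Population gives the same 24-hour requirement. Description of the Acts Performed and Devices Used describes the 63 participants as "patients on mechanical ventilation in intensive care with dyspnea". The Respiratory Parameters begins the Day 0 recording set-up with "The subject being connected to the ventilator".

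**First endpoint.** Secondary Objectives lists "the cumulative incidence of mechanical ventilation, the failure to wean from mechanical ventilation on D28" among the outcomes for the 28 days after inclusion. Secondary Endpoints and Research Follow-Up Visits also list the cumulative incidence of ventilation. Secondary Judgment Criteria fixes the method: "Cumulative incidence of mechanical ventilation on D28: The cumulative incidence estimates will be made using the gray method", compared with a Gray test.

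**Second endpoint.** Secondary Endpoints words it as "Proportion of patients with mechanical ventilator dependance beyond D28". Secondary Judgment Criteria words it as "Proportion of patients who failed to withdraw from mechanical ventilation on D28", with each experimental arm tested against placebo by Fisher test at 0.05. Secondary Objectives speaks of failure to wean (the quotation above).

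**Data.** Research Follow-Up Visits collects death, ventilation status (spontaneous or mechanical) and "withdrawal (in progress, successful, failure) until D28". Death by D28 is also an endpoint in its own right, with Fisher tests and Kaplan-Meier curves.

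**The concern.** A cumulative incidence curve describes the accumulation of first events in people who have not yet had the event at the time origin. Here the named event is the state that qualifies a patient for the trial. An endpoint met by everyone at the origin carries no information about treatment.

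It can be rescued only by supplying a different event, and the two natural candidates point in opposite directions. If the event is liberation from the ventilator, a higher curve is better. If it is return to the ventilator after weaning, a higher curve is worse. If the choice stays open until outcomes are known, it could be made after seeing which version looks favourable.

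The weaning-failure endpoint raises a lesser issue. Mortality by D28 is itself an endpoint in these patients with ARDS, so some deaths before D28 must be expected. Whether such a patient is a failure, a non-failure or excluded depends on which of the three wordings is followed, and that can change the size and even the direction of the contrast.

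**Working it through.** **1. The plan's own figure.** The article states no rate for either ventilation endpoint, so there is nothing to reproduce for them. Its one sample-size figure concerns the primary endpoint. With a difference of 1, SD 1, alpha 0.025 two-sided and 80% power, the two-sample t-test needs 20.32 per group, rounded up to 21, or 3 × 21 = 63. Power at 21 per group is 81.5%. The stated figure reproduces and is not touched by this point.

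**2. The cumulative incidence as worded.**

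- Time origin: inclusion, Day 0, since follow-up is the 28 days after inclusion.
- Event as named: mechanical ventilation.
- Status at the origin: every patient has had at least 24 h of ventilation.
- Estimate at Day 0: 21/21 = 100% in each arm, 63/63 = 100% overall.
- Number still at risk after Day 0: 21 − 21 = 0 per arm.

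Gray's test compares how events accrue over follow-up in those still at risk. With no one at risk there is no contrast to test. As a cross-check, a Fisher test of 21/21 against 21/21 gives p = 1.0.

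**3. Could the surrounding text supply another event?** Secondary Objectives, Secondary Endpoints, Research Follow-Up Visits and Secondary Judgment Criteria all carry the same label. None mentions liberation or re-ventilation as the event, and none names a competing event.

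**4. The three wordings of weaning failure, applied to a patient who dies before D28.**

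| Section | Idea | Patient who died before D28 |
|---|---|---|
| Secondary Objectives | failure to wean on D28 | could be counted as a failure |
| Secondary Endpoints | dependence beyond D28 | cannot be dependent beyond D28, so leans to not counted |
| Secondary Judgment Criteria | failed to withdraw on D28 | could be counted as a failure |

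**5. Does the choice matter? An assumed example.** The article gives no death or weaning rates. These counts are chosen only to show the mechanism. Per arm of 21, the experimental arm has 8 deaths and 2 still ventilated; placebo has 4 deaths and 5 still ventilated.

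| Treatment of deaths | Experimental | Placebo | Fisher p |
|---|---|---|---|
| Non-failures | 2/21 = 9.5% | 5/21 = 23.8% | 0.41 |
| Excluded | 2/(21 − 8) = 2/13 = 15.4% | 5/(21 − 4) = 5/17 = 29.4% | 0.43 |
| Failures | (8 + 2)/21 = 10/21 = 47.6% | (4 + 5)/21 = 9/21 = 42.9% | 1.00 |

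The direction reverses between the first and third rows. None of the three contrasts is significant at 0.05.

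**The case against.** **The label may be shorthand.** Gray's method is a competing-risk tool, and the follow-up data on ventilation and weaning status would support an event that varies after Day 0, such as the end of ventilation or a return to it. The authors may well have had one of these in mind. This stands to a degree: the literal 100% reading is probably not what they intended, and it would go too far to say that no usable analysis could be made from these data. But the intended event appears in none of the four sections that list the endpoint. Nor is this merely detail left to a fuller document, because the article itself names the event, estimator and test, and the named event conflicts with its own entry criterion.

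**Deaths.** A reader might infer that the weaning-failure proportion treats deaths as non-failures and so rewards an arm in which more patients die. The article does not support this. Only the dependence wording leans that way; the other two can include deaths, and no section gives a rule. Silence on how deaths are classified is something a condensed article may leave to the full protocol or SAP. Death by D28 is also analysed separately, so excess deaths would be reported beside the weaning result. What remains is the inconsistency of wording. The example above rests on invented counts and is not a forecast.

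**Importance.** These are secondary endpoints in a self-described pilot of a single 30-minute session. That is correct and limits the severity.

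**Conclusion.** The point on the cumulative incidence holds as worded: 63/63 = 100% at Day 0, the same in every arm, with no one at risk and nothing for Gray's test to compare. It rests on taking the named event literally and on inclusion as the time origin; no section offers another event.

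The point on weaning failure holds only as an inconsistency between three wordings that can classify deaths before D28 differently. Its size cannot be estimated from the article, and the claim that deaths are counted as non-failures is not made out.

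The primary endpoint (the change in MDP-A1 around the session) and the 21 per group are unaffected. Severity is moderate or lower.

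**What to change.** **Cumulative incidence.** In Secondary Objectives, Secondary Endpoints, Research Follow-Up Visits and Secondary Judgment Criteria, replace the endpoint by the cumulative incidence of liberation from mechanical ventilation from Day 0 to D28, with death as the competing event, estimated by arm and compared by Gray's test. If the sponsor meant another event, such as re-ventilation, state that event, its time origin and its competing event instead. Settle this before outcome data are examined.

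**Weaning failure.** Use one wording in Secondary Objectives, Secondary Endpoints and Secondary Judgment Criteria, and say how a death before D28 is classified. Show deaths alongside the result, for example as a table by arm of dead, still ventilated, and alive and off ventilation at D28. A composite of dead or still ventilated is one acceptable definition; separate reporting of death and weaning is another.

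**Cost.** Rewording only. Ventilation status, weaning status and death are already collected to D28 under Research Follow-Up Visits, and the sample size does not change.

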### Research Calendar

The total duration planned for the study is 12 months. The total duration of participation for each patient is 28 days; because each patient will be followed up for a period of 28 days after inclusion in order to collect the evolution data. The Table 1 summarizes the research chronology.

**Table 1 T1:** Summary of the research chronology.

**Actions**	**Day 0 (inclusion, before tDCS)**	**Day 0 (after tDCS)**	**Day 1 to Day 27**	**Day 28 (after tDCS)**
information	*X*			
Informed written consent	*X*			
Background	*X*			
SAPS-II score	*X*			
SOFA score	*X*			
Clinical and neurological examination	*X*	*X*	*X*	*X*
Glasgow score	*X*	*X*	*X*	*X*
RASS score	*X*	*X*	*X*	*X*
FOUR score	*X*	*X*	*X*	*X*
CAM-ICU score	*X*	*X*	*X*	*X*
Ventilation status	*X*	*X*	*X*	*X*
Ventilation weaning status (in progress, successful, failed)			*X*	*X*
Multidimensional dyspnea profile	*X*	*X*		*X*
IC-RDOS scale	*X*	*X*		*X*
EEG for PPI assessment	*X*	*X*		*X*
Respiratory Function Evaluation: PaO2, PaCO2, Mouth pressure, PetCO2, Tidal volume (VT), Respiratory frequency (F), Ventilation/minute (calculated from VT and F)	*X*	*X*		*X*

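### The inverted Kaplan-Meier estimator named for median ICU stay estimates follow-up time (28 days by design), not stay, and the log-rank test paired with it does not compare that quantity

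*Protocol article*

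**What the plan says.** The Secondary Endpoints section of the protocol article lists "The duration of the resuscitation stay" among the 28-day outcomes. Under Secondary Judgment Criteria the method is fixed: "Estimates of the median length of stay in intensive care will be made from an inverted Kaplan Meier estimator", then "compared according to the previous procedure using a log rank test". The section does not define the word inverted, name the event, or say how a death in ICU enters this analysis.

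Three other statements bear on it:

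- Follow-up is fixed. Research Calendar says "each patient will be followed up for a period of 28 days after inclusion", and Research Follow-Up Visits agrees.
- ICU death within that window is an outcome in its own right: "Death by D28 in intensive care and in the hospital".
- For delirium and for mechanical ventilation, Secondary Judgment Criteria plans a competing-risk method: "The cumulative incidence estimates will be made using the gray method and compared according to the previous procedure using a gray test". Length of stay is the time-to-event duration in that list that gets a different tool.

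**The concern.** The inverted or reverse Kaplan-Meier is a standard device for describing follow-up. It codes the censored patients as events and the patients who had the event as censored, so its median is the median potential follow-up. It answers how long patients could have been observed, not how long they stayed in ICU. Where every patient has the same 28-day horizon, that answer is set by the design before any data exist.

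An analyst who applies the named method literally would report a figure near 28 days in each arm. It would carry almost no information about stay and could not show a difference between arms. The log-rank test beside it either tests something else (the rate of leaving ICU) or, on the reversed coding, tests the follow-up distribution. Either way, the reported median and p-value would not describe ICU stay together.

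This is not a detail left to an unseen analysis plan: the article names a specific estimator for a specific endpoint.

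**Working it through.** **Plan's own figure.** None is stated for length of stay. The only computable figure is 21 per group for the primary endpoint (difference 1, SD 1, alpha 0.025, power 80%). It reproduces: the two-sided t-based solution is 20.32, rounded up to 21. It is used below only as the arm size.

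**Inputs.** From the documents: cut-off at day 28 and 21 patients per arm. Assumed, because the documents give no rates: exponential time to the end of ICU stay with mean m = 10, 14 or 20 days; a share p = 0, 20, 30 or 40% of stays ending in death; time counted from inclusion. Each scenario used 40,000 simulated patients, with times rounded up to a quarter day.

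**Step 1: true median stay, any cause of ending.** Median = m × ln 2: 10 × 0.693 = 6.9; 14 × 0.693 = 9.7; 20 × 0.693 = 13.9 days. Simulated: 7, about 10, and 14.

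**Step 2: reversed estimator, discharge and death both ending the stay.** After the swap, the only events are patients still in ICU at day 28. The curve stays at 1 until day 28 and then falls to 0, so the median is 28 whenever at least one patient is still there. With m = 14, the chance that none of 21 is still there is (1 − e^(−28/14))^21 = 0.8647^21 = 0.047. The median is therefore 28 in about 95% of trials and not reached in the other 5%. Simulation at n = 21 gave 95.35% and 4.65%.

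**Step 3: reversed estimator, deaths coded as censored before the swap.** Deaths then become events. Their hazard is p/m, so the median is the smaller of 28 and m × ln 2 / p. For m = 10, p = 30%: 6.93/0.3 = 23.1. For m = 10, p = 40%: 17.3. For m = 14, p = 40%: 9.70/0.4 = 24.3. In the other scenarios it is capped at 28.

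| Mean stay | ICU deaths | True median stay | Reversed, Step 2 | Reversed, Step 3 | Alive discharge reaches 50% |
|---|---|---|---|---|---|
| 10 | 20% | 7 | 28 | 28 | 10 |
| 10 | 30% | 7 | 28 | 23.25 | 13 |
| 10 | 40% | 7 | 28 | 17.25 | 18.25 |
| 14 | 20% | 10 | 28 | 28 | 14 |
| 14 | 30% | 9.75 | 28 | 28 | 17.5 |
| 14 | 40% | 9.75 | 28 | 24.25 | 24.75 |
| 20 | 20% | 14 | 28 | 28 | 19.5 |
| 20 | 30% | 14 | 28 | 28 | 24.75 |
| 20 | 40% | 14 | 28 | 28 | not reached |

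With no deaths, both reversed versions give 28 for each mean. Step 2 thus gives 28 in 12 of 12 scenarios. Step 3 gives 28 in 9 of 12 and about 17 to 24 days in the other three. None of these figures estimates stay.

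**Step 4: the log-rank test.** On the Step 2 coding, all events fall on day 28 and everyone then at risk has the event. With d = n at risk, the expected count in an arm is d × n1/n = n1, equal to the observed count. The variance contains the factor (n − d) = 0. The statistic is 0/0, so nothing is compared. On the ordinary coding, the test compares the rate of leaving ICU, which is not what the reversed median shows.

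**Step 5: if inverted only means 1 minus Kaplan-Meier.** The median is then the ordinary one. With death counted as the end of stay it is Step 1, a valid duration. With deaths censored it is m × ln 2/(1 − p); for m = 14 and p = 30%, that is 9.70/0.7 = 13.9 days. Discharge by D28 would read 1 − e^(−0.7 × 2) = 75%, against a true alive-discharge incidence of 0.7 × (1 − e^(−2)) = 61%.

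**The case against.** The strongest reply is that this is a slip of translation. The English is visibly translated, and a median stay paired with a log-rank test fits an ordinary Kaplan-Meier curve, or its complement, better than a reversed one. On that reading, with death counted as the end of stay, the method is sound (Step 1). This is plausible and cannot be excluded. It does not rescue the text, because the words as printed name an estimator of follow-up, and someone else may have to carry out the plan.

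Three stronger readings are tempting, and the document supports none of them.

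- *That ICU deaths are censored.* No section says so. Duration of stay can equally mean time to leaving ICU for any reason, and then there is no competing-risk fault. Overstated discharge (Step 5) follows only if deaths are censored. The event definition is the kind of detail an article may leave to the full protocol.
- *That the result is always 28 days.* This holds when discharge and death both end the stay and someone is still in ICU at D28. If deaths become events, the median depends on the death rate: with a mean time to death of 40 days it is 40 × ln 2 = 27.7, and with 30 days it is 20.8.
- *That the ventilation endpoint rewards early death.* Secondary Endpoints lists "Proportion of patients with mechanical ventilator dependance beyond D28", and a reader might infer that an early death counts as a success. Secondary Judgment Criteria instead describes failure to come off the ventilator by D28, under which a patient who dies ventilated may count as a failure. No section fixes the coding, so this is not an established error.

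It is also fair that a median equal to the follow-up limit would probably be noticed, and that this is one secondary outcome in a study that calls itself a pilot.

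**Conclusion.** The point holds in limited form. Read in its usual sense, the estimator named for median ICU stay does not estimate stay. It returns about 28 days in each arm when discharge and death both end the stay, and a mixture of time to death and cut-off if deaths become events. The paired log-rank test does not compare that quantity.

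The 28-day result in Step 2 follows from the fixed follow-up and needs only that someone in the arm is still in ICU at D28. The other figures rest on assumed exponential stays, assumed death shares and a clock starting at inclusion; they show direction and rough size, not a forecast. If the clock started at ICU admission, the number would shift by the stay before inclusion, but it would still measure follow-up.

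It cannot be said that the reported median would certainly be wrong, since the word may have been meant as 1 minus Kaplan-Meier. The consequence is confined to one secondary endpoint: the primary analysis and N = 63 are untouched. It should be corrected before the analysis.

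**What to change.** In Secondary Judgment Criteria, delete the inverted Kaplan-Meier for ICU stay. Replace it with the cumulative incidence of ICU discharge alive up to D28, with death in ICU as competing event and patients still in ICU at D28 censored there. Compare each experimental arm with placebo by Gray's test, as already planned for delirium and ventilation. Report the median as the day the curve reaches 50%, and state that it was not reached where that applies.

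An acceptable alternative is an ordinary Kaplan-Meier of time to the end of ICU stay from any cause, with a log-rank test. The text must then say that death counts as the end of stay, and the result must be read beside mortality, because early deaths shorten the stay on this measure. The two answer different questions, so one should be named before outcomes are seen.

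The cost is a change of wording and of one analysis program. Research Follow-Up Visits already provides for collecting deaths and ICU length of stay to D28. No extra patients, visits or measurements are needed.
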